**Table 2 T2:**
[figure not shown]
Participant timeline.

**Table 3 T3:**

Bedside protocol for the ACU-SIM study.

#### Patient follow-up

2.8.7

After the subject is discharged from the ICU, the researcher will not perform any form of intervention. According to the requirements of the observation indicators and their time points, follow-up data collection and filling will be performed 28 days, 90 days, 6 months and 1 year after ICU admission; patients will be followed until the follow-up time expires or the subject dies. The follow-up data collection includes the incidence of time-to-event, the FIM^TM^ scale and so on. Follow-up will be conducted by clinic follow-up and telephone follow-up. The investigator will notify the patient to return to the clinic for follow-up at a fixed time point. If it is inconvenient for the patient to go to the clinic, the follow-up will be conducted over the phone. If the patient refuses to proceed and asks to quit at any time during the follow-up, is the patient will be withdrawn from the study. If the patient cannot be contacted more than 3 times during the follow-up period, by any contact method (including telephone, mail, and various social software), is the patient will be considered lost to follow-up.

### Recruitment

2.9

Ninety-eight subjects will be needed over the timeline of 2 years according to our sample size calculation. Within 24 hours of admission to the ICU, the patient will be screened against the inclusion criteria. The signing of an informed consent form for inclusion in the study will be performed once the patient or next-of-kin agrees to participate in the study. Data will be assessed only by the researchers, and all data will be kept confidential. Patient recruitment will begin in November 2019, and the expected completion date of the study is December 2022.

### Statistical analysis

2.10

All available data will be analyzed descriptively. For continuous data, the normality test will be applied at the very beginning of the analysis. We will bewrite the results as the means, standard deviations, and 95% confidence intervals (CIs) for continuous data that conform to the normal distribution; medians, quartiles, and ranges for rank data and continuous data that do not fit the normal distribution; and percentages for discrete data.

The change in the RF_CSA_ from baseline will be analyzed by a generalized additive mixed model of repeated measures design. Analysis of the time-to-event outcome (at day 28, day 90, six months, and 1 year after the admission of ICU) will be conducted by applying Kaplan-Meier curves. Kaplan-Meier survival curves will be performed to describe the survival rate between the 2 groups, and the log-rank method will be used to compare the survival rates of the acupuncture group and control group. Multivariate Cox proportional hazard regression models will be used to analyze several constituents (such as acute physiology and chronic health evaluation-II, SOFA score, demographic and diagnostic data), adjust for covariates, and correct for confounding. Our team will use similar approach mentioned above to analyze secondary outcome measures when they can be expressed as time-to-event outcome dimensions. All regression analyses (generalized additive mixed models, log-rank analysis, multivariate Cox proportional hazard regression models) will include the same covariates as the primary analysis. If there are any measurable differences between the 2 study groups with regard to prognostic factors, a propensity score analysis will be applied to assess the sensitivity of the results to any treatment allocation biases. The propensity score will be set for the main outcome. After the 2 sets of data are analyzed according to the previous analysis, the patients will be matched with the propensity score, and then the main outcomes of the matched 2 groups will be compared again to see if there are any similarities or differences between the 2 groups before and after the match. If they are the same, the results are stable; however, a difference means that there are factors affecting the evaluation of the outcome before the match, and these factors will need to be explained.

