### Sample size

2.3

Temporarily, there are no data on how acupuncture benefits patients with SIM. Therefore, we searched for related studies. In the trial “Electrical muscle stimulation prevents critical illness polyneuromyopathy.”^[19]^ the incidence rates were 12.5% in the EMS group and 39.3% of the control group. Assuming α = 0.05 and 1-β = 0.8, and an experimental group to control group ratio of 1:1, the sample size was calculating by STATA software (STATA IC 15.0, Stata Corp, College Station, TX). We will need 39 patients in the experimental group and 39 patients in the control group. Considering factors such as dropouts, the sample size of the acupuncture group and the control group is designed to be 49 and 49, respectively; a total of 98 cases will be observed.

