### Study groups

2.7

Since this study is a real-world study, the grouping of the study subjects was determined by the actual observations. Therefore, no randomization of groups was set in this study. The subjects will be as allocated into 2 arms.

Group 1: acupuncture group

When the participant meets the inclusion criteria (1 to 5), the acupuncturist will assess the conditions for patient treatment. Patients can enter this group and have acupuncture treatment if they do not have specific conditions (such as edema, coagulopathy, acupoints local skin and soft tissue infection, and rejection of acupuncture treatment) that are not suitable for acupuncture.

Group 2: control group

Patients who are not suitable for acupuncture or are not willing to receive acupuncture could enter this group. In addition to basic treatment, patients in this group will be prescribed exercises, such as early in-bed activities or wheelchair activities.

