### Missing data

2.11

There are repeated measurement data (including RF_CSA_) in our research, and some data may be missing during the experiment. RF_CSA_ is 1 of the primary outcome indicators; if the baseline RF_CSA_ (the first measured value) is missing, no interpolation will be performed. In other situations, we will deploy a diagnostic analysis related to missing data. The ratio of missing data will be summed in each group and at each time point, and the threshold of this ratio is set to 5%. If the missing data is above the threshold, the Little test will be conducted. Otherwise, a specified primary and/or secondary outcome has less than 5% of missing data, a complete case analysis without interpolating the missing values. We will then analyze the complete cases without data imputation if the complete case value is implied to be a random missing by Little test. When Little's test betokens that the complete case data set is not a random missing, the threshold estimates and their 95% CIs will be proclaimed after implementing a worst- and best-case scenario imputation for the missing values. Multiple imputations (MI) will not be performed if the worst- and best-case analyses concede for the same conclusion. Oppositely, statistical software will create ten MI data sets beneath the hypothesis of data missing at random. After MI, our research team will pool the results of the trial of the intervention effect and 95% CI of the analyses of each data set.

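### Name baseline RF_CSA as a covariate, and fix the scale of change, in the primary mixed model: a cheap safeguard for groups that are not randomised

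*Protocol article*

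**What the plan says.** RF_CSA decline is one of three primary outcomes (protocol article, section 2.8). Its analysis is given in section 2.10: "The change in the RF_CSA_ from baseline will be analyzed by a generalized additive mixed model of repeated measures design". The article does not say whether change is in area or in percent. The one scale it attaches to RF_CSA decline elsewhere is percent: eligibility needs a fall of more than 9.24% (sections 2.4.3 and 2.4.4).

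The covariates appear in the Cox sentence of section 2.10, as an open list: "such as acute physiology and chronic health evaluation-II, SOFA score, demographic and diagnostic data), adjust for covariates, and correct for confounding". A later sentence gives every regression, the mixed model included, the covariates of the primary analysis. The mixed model is itself a primary analysis, so that rule is circular and closes no list.

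Baseline RF_CSA is defined, and is protected from imputation, in section 2.11: "if the baseline RF_CSA_ (the first measured value) is missing, no interpolation will be performed". It is not mentioned as a covariate.

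On allocation, section 2.7 says: "Therefore, no randomization of groups was set in this study". Patients who are unsuitable for acupuncture (edema and coagulopathy are among the examples) or unwilling to have it go to the control group. Section 2.10 adds propensity-score matching as a sensitivity analysis if the groups differ on prognostic factors, without listing the variables in the score.

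**The concern.** In a randomised trial, leaving the baseline value out of a change-score model mainly costs precision. Here allocation follows clinical suitability and preference, so mean starting area may differ between groups. If a muscle loses a roughly constant share of its area, the group with smaller muscles loses less area with no treatment effect at all. With smaller muscles in the acupuncture group this looks like a benefit; with larger ones it looks like harm or hides a benefit. Edema steers patients to control and might also alter a measured area. That last step is an inference, not something the article states.

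At stake is whether the RF_CSA result of this pilot, meant to inform a multicentre study, can be separated from a difference in starting muscle size.

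**Working it through.** **1. The plan's own figure.** Section 2.3 gives "Assuming α = 0.05 and 1-β = 0.8, and an experimental group to control group ratio of 1:1" and "the incidence rates were 12.5% in the EMS group and 39.3% of the control group". The unpooled two-proportion formula, two-sided, is n = (1.96 + 0.8416)² × [0.125 × 0.875 + 0.393 × 0.607] / (0.393 − 0.125)² = 38.02, so 39 per group. This agrees with "We will need 39 patients in the experimental group and 39 patients in the control group". An assumed dropout of 20% gives 39 / 0.80 = 48.75, so 49, which agrees with "the sample size of the acupuncture group and the control group is designed to be 49 and 49, respectively". The calculation is for a binary incidence. The article gives no SD, effect size or correlation for RF_CSA, so everything below rests on assumptions.

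**2. Possible bias on the absolute scale.** Assumptions: baseline mean 4 SD (coefficient of variation 25%), proportional loss with mean 20% and SD 5 percentage points in both groups, no treatment effect, acupuncture group smaller at baseline by d SD, 39 per group, one follow-up.

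- False benefit = 0.20 × d, that is 0.04, 0.06 and 0.10 SD for d = 0.2, 0.3 and 0.5.
- Variance of change within a group = 0.20² × 1 + 0.05² × (mean² + 1). For d = 0.5 this is 0.04 + 0.0025 × 17 = 0.0825 in control and 0.04 + 0.0025 × 13.25 = 0.0731 in acupuncture. The average is 0.0778, so SD = 0.279.
- Standard error = 0.279 × √(2/39) = 0.063, and 0.10 / 0.063 ≈ 1.6. A two-sided 5% test then rejects in about one trial in three.

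Simulation (3,000 to 4,000 trials per scenario in most runs) agrees:

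| d (SD) | False benefit (SD) | Rejection, unadjusted | Rejection, baseline in model |
|---|---|---|---|
| 0.2 | 0.04 | about 9% | about 5% |
| 0.3 | 0.06 | about 15% | about 5% |
| 0.5 | 0.10 | 33% to 36% across runs | 4% to 5% |

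**3. Scan error.** At d = 0.5, error of 0.2 or 0.4 baseline SD in each scan (5% or 10% of mean area) lowers unadjusted rejection to about 18% to 19% and 10%.

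**4. Percent change.** Under the same proportional loss, unadjusted percent change shows no bias and about 5% rejection. If loss does not depend on muscle size, the roles swap: absolute change is sound, and unadjusted percent change rejects in about 33% of trials at d = 0.5. The baseline-adjusted model stayed at about 5% to 9% in every scenario tried.

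**5. Power.** With equal SDs at both times and correlation ρ, the variance ratio of adjusted to change-score analysis is (1 − ρ²) / [2(1 − ρ)] = (1 + ρ)/2. If the change score had 80% power:

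| ρ | Variance ratio | Power with adjustment |
|---|---|---|
| 0.5 | 0.75 | 90% |
| 0.7 | 0.85 | 86% |
| 0.8 | 0.90 | 84% |
| 0.9 | 0.95 | 82% |

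A 0.5 SD imbalance inflates the adjusted variance by 1 + 0.5²/4 ≈ 1.06. Power is then about 88% at ρ = 0.5 and 80% at ρ = 0.9, so the gain can disappear.

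**The case against.** Four stronger readings are tempting, and the article supports none of them.

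- **That the plan leaves baseline RF_CSA out.** The covariate list is open and the carry-over rule is circular. Nothing excludes baseline RF_CSA from the model or from the propensity score, and a full list may sit in an analysis plan that is not shown. What stands is that the article sets out the response and a covariate rule for this model, and the one measurement most tied to that response is not named.
- **That the comparison is biased.** Bias needs an actual imbalance in starting area, and change on the chosen scale must depend on that area. No figure shows an imbalance, and the listed reasons for not treating are not muscle size. Percent change may be what is meant, and under proportional loss it needs no correction. This leaves a risk, not a demonstrated error.
- **That a known amount of power is lost.** No RF_CSA power is stated. The 80% is borrowed from a binary calculation and the correlations are assumed. The two sets of figures also describe different data: the bias simulation implies a correlation of about 0.97 and a smaller follow-up SD, whereas the power table assumes equal SDs.
- **That adjustment removes the bias.** Without randomisation, change-score and baseline-adjusted analyses rest on different assumptions (Lord's paradox). With scan error and loss unrelated to size, unadjusted absolute change was unbiased, while adjustment was off by 0.02 to 0.07 baseline SD at a 0.5 SD imbalance.

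Propensity matching is a partial safeguard. It is conditional, is a sensitivity analysis only, and helps here only if baseline RF_CSA is in the score.

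A high correlation does not dispose of the concern. Under proportional loss the slope of follow-up on baseline is 0.8, so the gap between unadjusted and adjusted results is 0.2 times the imbalance even at a correlation of about 0.97.

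**Conclusion.** The point holds as a cheap improvement, not as an established error. Section 2.10 leaves open both the scale of change and the place of a baseline value that is already collected, in a design that does not balance that value. Under the assumptions shown, an imbalance of 0.2 to 0.5 SD could produce a false benefit of 0.04 to 0.10 baseline SD and about 9% to 33% false rejection at a nominal 5% on the absolute scale, less with scan error. With balanced groups there is no such bias. Choosing percent change moves the risk to the case where loss is not proportional. Adjustment was the most stable choice across the scenarios, with a small residual bias when scans carry error. The power argument is secondary and cannot be tied to any RF_CSA power in the article.

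**What to change.** In section 2.10:

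1. State whether the primary RF_CSA response is absolute or percent change, and report the other scale as a sensitivity analysis.
2. Include baseline RF_CSA (the value from which change is computed) and its interaction with time in the mixed model, with only post-baseline scans as responses.
3. Name baseline RF_CSA among the propensity-score variables.
4. Replace the circular covariate rule with a named list.

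The cost is a few sentences and one or two degrees of freedom, with no new data. The text should also acknowledge that scan error leaves a small residual bias and that, without randomisation, baseline adjustment is not guaranteed to remove all confounding.

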**Methods::**

The ACU-SIM pilot study is a single-center, propensity-score stratified, assessor-blinded, prospective pragmatic controlled trial (pCT) with a 1-year follow-up period. This study will be deployed in a multi-professional critical care department at a tertiary teaching hospital in Guangzhou, China. Ninety-eight intensive care unit subjects will be recruited and assigned to either the control group or the acupuncture group. Both groups will receive basic treatment for sepsis, and the acupuncture group will additionally receive acupuncture treatment. The primary outcomes will be the rectus femoris cross-sectional area, the Medical Research Council sum-score and time-to-event (defined as all-cause mortality or unplanned readmission to the intensive care unit due to invasive ventilation). The activities of daily living will be accessed by the motor item of the Functional Independence Measure. Recruitment will last for 2 years, and each patient will have a 1-year follow-up after the intervention.

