#### Inclusion criteria

2.4.3

(1)Age 18 to 85 years old;(2)Met the criteria of Sepsis 3.0^[20]^, which defines sepsis as infection + sequential (sepsis) organ failure assessment score (SOFA) ≥ 2 points within the first 24 hours;(3)First ICU admission and the patient should be expected to survive within the first 48 hours;(4)Informed consent was signed by the patient or their next to kin;(5)The RF_CSA_ decreased more than 9.24%^[21]^ after ICU admission;(6)Alive during the ICU stay.

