#### Exclusion criteria^[1,2]^

2.4.4

(1)A confirmed pregnancy or the urine β-HCG test is positive;(2)The questionnaires (MRC-SS and FIM^TM^) or consent form could not be completed due to cognitive abnormalities.(3)A newly diagnosed primary neuromuscular disease when admitted to the hospital;(4)Leg amputation, pelvic/femoral fractures or knee/hip replacement that prevent the measurement of the RF_CSA_;(5)Malnutrition (BMI less than 18.5 kg/m^2^) or cachexia;(6)Metastatic tumors (PD) or ongoing chemotherapy;(7)Cardiorespiratory arrest or imminent death;(8)Long-term corticoid treatment;(9)Could not walk independently before sepsis onset;(10)ICU length of stay (LOS) < 7 days^[2]^;(11)Sepsis onset more than 5 days before ICU admission^[2]^;(12)Therapy withdrawal or consent refusal.

Patients are eligible if they are diagnosed with sepsis, their RF_CSA_ decreased more than 9.24%^[21]^ from baseline, and informed consent has already acquired from the patient and/or immediate family member. A case report form (CRF) will be completed, and the RF_CSA_, MRC-SS score and other relevant data will be obtained, for all eligible and consenting patients. We will use the RF_CSA_ to assess the changes in muscle morphometry; the MRC-SS will be used to assess whether patients meet the diagnostic criteria of ICU-acquired weakness and to observe mortality, rehospitalization, reintubation and mechanical ventilation and other relevant indicators during the 1-year follow-up.

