### Outcome

2.8

The primary outcomes will be the decline of RF_CSA,_ the MRC-SS and time-to-event (defined as all-cause mortality or unplanned readmission to the ICU due to invasive ventilation). The activities of daily living will be accessed by the motor item of the Functional Independence Measure (FIM^TM^). Secondary outcome includes the expression level of MSTN, ICU length of stay, length of hospital stay, duration of invasive/non-invasive mechanical ventilation. The outcomes will be measure as follow:

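### Reading death-or-ICU-readmission from ICU admission counts index-stay time in which readmission cannot occur, so the day-28 comparison can reflect ICU length of stay

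*Protocol article*

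**What the plan says.** Section 2.8 names as a primary outcome "time-to-event (defined as all-cause mortality or unplanned readmission to the ICU due to invasive ventilation"). Section 2.10 sets its horizons: "Analysis of the time-to-event outcome (at day 28, day 90, six months, and 1 year after the admission of ICU"). Section 2.8.7 uses the same clock: "follow-up data collection and filling will be performed 28 days, 90 days, 6 months and 1 year after ICU admission". The Abstract's Methods paragraph words it differently: "each patient will have a 1-year follow-up after the intervention".

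The groups are compared with Kaplan-Meier curves, Cox models and a log-rank test: "the log-rank method will be used to compare the survival rates of the acupuncture group and control group". Section 2.10 mentions no discharge origin, delayed entry or landmark.

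Three eligibility rules bear on when an event can occur:
- Inclusion criterion 3: "First ICU admission and the patient should be expected to survive within the first 48 hours". The index stay is therefore the first ICU stay, and a readmission needs a discharge from it.
- Inclusion criterion 6: "Alive during the ICU stay". Section 2.8.6 treats patients who meet criteria 1 to 6 as those who survived and left the ICU.
- Exclusion criterion 10: "ICU length of stay (LOS) < 7 days".

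ICU length of stay is itself a secondary outcome (section 2.8).

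**The concern.** A patient still ventilated in the ICU on day 28 is event-free for readmission only because readmission is not yet possible. A patient discharged on day 10 has had 18 days in which to be readmitted. By a fixed day from admission, the event count therefore mixes the risk after discharge with the length of the index stay.

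The two groups may well differ in that length. Treatment may change it, and allocation is not random: section 2.7 sends patients unsuitable for acupuncture, for example with edema or coagulopathy, to the control group. The Cox covariates named in section 2.10 adjust for baseline severity, not for time in which no event is possible.

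If one group leaves the ICU sooner, which would usually be read as a benefit, it looks worse on this outcome at day 28. Day 28 is a named horizon of a primary outcome in a pilot meant to inform a multicenter study.

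**Working it through.** **The plan's own figure.** The only design calculation (section 2.3) uses incidences of 12.5% and 39.3%, α = 0.05 (taken as two-sided) and power 0.80. With unpooled variance, n = (1.960 + 0.842)² × (0.125 × 0.875 + 0.393 × 0.607) / 0.268² = 38.02, rounded up to the stated 39 per group. It reproduces, but it concerns polyneuromyopathy. The article gives no event rate for the composite and no ICU stay by group, so both are assumed below.

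**Step 1: share of the window in which no event can occur.** From exclusion criterion 10 the stay is at least 7 days. At day 28 the share is 7/28 = 25% at minimum, 14/28 = 50% for a 14-day stay and 20/28 = 71% for a 20-day stay. At day 90 it is 7/90 = 8% to 20/90 = 22%.

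**Step 2: event probability under equal risk.** Take ICU survivors, a fixed stay L, and the same constant post-discharge hazard h in both groups:

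P(event by day t from admission) = 1 − exp(−h(t − L)).

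Assume a one-year risk of 40%, so h = −ln(0.6)/365 = 0.0014 per day.

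| Day from admission | L = 10 | L = 14 | L = 20 | Ratio 10 vs 14 | Ratio 10 vs 20 |
|---|---|---|---|---|---|
| 28 | 2.5% | 1.9% | 1.1% | 1.28 | 2.23 |
| 90 | 10.6% | 10.1% | 9.3% | 1.05 | 1.14 |
| 182 | 21.4% | 21.0% | 20.3% | 1.02 | 1.05 |
| 365 | 39.2% | 38.8% | 38.3% | 1.01 | 1.02 |

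The ratios hardly depend on h. For small h they tend to (28 − 10)/(28 − 14) = 1.29 and (28 − 10)/(28 − 20) = 2.25 at day 28. Assumed one-year risks of 20% and 60% give nearly the same ratios. With a front-loaded hazard (Weibull shape 0.5, 40% one-year risk), stays of 10 versus 20 days give 10.7% versus 7.3% at day 28 and 39.6% versus 39.1% at one year.

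**Step 3: log-rank error with no true difference.** Simulation with 39 per group, stay = 7 days plus an exponential, and post-discharge hazard 0.02 × exp(−t/30) per day in both groups.

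| Mean stays | Clock and horizon | Rejection at nominal 5% |
|---|---|---|
| 12 vs 22 days | admission, day 28 | about 15% (events about 21% vs 13%) |
| 12 vs 22 days | admission, day 90 | about 6% |
| 12 vs 22 days | admission, one year | about 5 to 6% |
| 12 vs 14 to 12 vs 16 days | admission, day 28 | about 5 to 7% |
| 12 vs 22 days | discharge, day 28 | about 5% (events about 31% in both) |

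A second simulation (49 per group, the front-loaded Weibull hazard, mean stays 12 versus 20 days) gave 9.0% at day 28, 6.0% at day 90 and 4.8% at one year. The corresponding hazard ratios were 1.51, 1.07 and 1.02. With discharge as origin they were 0.98 to 1.00.

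**The case against.** **The one-year result is barely affected.** This stands. The design is described by its one-year follow-up, and there the ratio is 1.01 to 1.03. A reader might infer that the whole time-to-event comparison is biased; the calculations do not support that.

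**The large figures need large assumptions.** This also stands. The 15% error needs a 10-day difference in mean stay. If stays are equal, the effect is nil. Wide absolute gaps at day 28 can be produced with a constant hazard of 1% per day: 1 − exp(−0.01 × 18) = 16.5% versus 1 − exp(−0.01 × 8) = 7.7% for stays of 10 and 20 days. But that hazard implies 1 − exp(−0.01 × 355) = 97% with an event by one year. At 40% one-year risk and constant hazard, the same gap is 2.5% versus 1.1%.

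**Section 2.10 fixes horizons, not the Kaplan-Meier origin or risk set, and a separate analysis plan may do so.** Partly stands. Admission is the natural reading of sections 2.10 and 2.8.7, but the article does not say outright that every patient enters the risk set at admission, and the Abstract uses another clock. The admission-based horizons are stated, however, so an event count by day 28 carries the problem whatever the risk-set details.

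**Death in the ICU may count after all.** Group entry uses criteria 1 to 5 (sections 2.5.1 and 2.7) and follow-up runs until death. If ICU deaths are kept, admission or group entry is a proper origin for death, and only the readmission component is affected. That the whole index stay is event-free for the composite holds only with criterion 6 as written.

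**Event-free status by a fixed day is a legitimate total-effect measure.** It can be when ICU deaths count. Among ICU survivors it is not a measure of readmission risk.

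**Conclusion.** The concern holds, mainly for day 28. On the document's own rules, readmission cannot occur in the index stay, and under criterion 6 death there cannot count. For equal post-discharge risk, the shorter-stay group then shows more day-28 events, by a ratio of about 1.3 (10 versus 14 days) to 2.2 (10 versus 20 days). Log-rank error is about 15% for a 10-day difference in mean stay and about 5 to 7% for 2 to 4 days. The distortion is small at day 90 and negligible at six months and one year.

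These sizes rest on assumed stays and hazards. A reader might also infer that the acupuncture group in particular will be penalised. The documents do not support this, because they give no stay by group and do not show which group will leave the ICU sooner.

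**What to change.** In section 2.10:

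1. Report the two components separately. Count readmission from index ICU discharge, or on the admission scale with delayed entry at discharge, with death as a competing event. Choose one in advance, since the two can differ if risk is concentrated soon after discharge. State that patients still in the index stay are not at risk of readmission.
2. Report all-cause death on its own clock, from ICU admission or group entry.
3. While the analysed population is ICU survivors, use the same discharge entry for the composite.
4. Do not interpret the day-28 composite counted from admission as a treatment effect on readmission.
5. Reconcile the follow-up clock in the Abstract with sections 2.8.7 and 2.10.

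This changes analysis wording only; ICU length of stay and follow-up events are already collected. There are two costs. First, the discharge-based analysis conditions on surviving and leaving the ICU, which happens after treatment starts. It does not remove that selection and must be read alongside the mortality result. Second, with the last visit one year after admission, a patient with a 20-day stay has 365 − 20 = 345 days of follow-up from discharge, so a full year on the discharge clock is not covered.

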#### Collecting healthcare data within the ICU stay

2.8.6

During the screening period, the relevant subject information will be completed, and baseline demographic-related items will be collected. The SOFA score, the immediate acute physiology and chronic health evaluation II score (and SAPS score), the GCS score, body temperature, mechanical ventilation or not, the infection site, the pathogenic examination before the administration of antibiotics or use of vasoactive drugs, arterial blood gas analysis, blood routine, coagulation function, liver function, kidney function, heart function, infection index, urine pregnancy test (female subjects), and an electrocardiogram will be recorded during this period. The length of the first antibiotic use and whether the pathogen is sensitive to the antibiotic will be recorded after initiation.

For patients who survive and are discharged from the ICU - meeting all inclusion criteria (1 to 6) - the mechanical ventilation duration time, LOS, total hospital stay, sum sedative analgesic dose, statin dose, blood glucose level, insulin dosage, glucocorticoid dosage, protective constraints, and the duration of neuromuscular blockers will be additionally recorded.

Table 2 shows a general view of the data collecting and the time of acquisition for each item. We will manage all study data anonymously, and all CRFs will be labelled with a study number allocated to each individual participant. The CRF will be in both paper and electronic formats. The paper version of the CRF will be used for backup storage of data and for verification when needed. The daily management of data will be completed on the EDC system. And the details of bedside data collection are shown in Table 3.

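### Kaplan-Meier does not carry over from the primary composite to length of hospital stay, because patients who leave the ICU alive can still die on the ward before discharge

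*Protocol article*

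**What the plan says.** Section 2.10 describes the composite of all-cause death or unplanned ICU readmission with Kaplan-Meier curves. For the group comparison, "the log-rank method will be used to compare the survival rates of the acupuncture group and control group". For adjustment, "Multivariate Cox proportional hazard regression models will be used to analyze several constituents". It then extends this to other endpoints: "Our team will use similar approach mentioned above to analyze secondary outcome measures when they can be expressed as time-to-event outcome dimensions".

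Section 2.8 lists the secondary outcomes: "Secondary outcome includes the expression level of MSTN, ICU length of stay, length of hospital stay, duration of invasive/non-invasive mechanical ventilation". Myostatin level is not a time, so the extension can only refer to the three durations, although 2.10 names none of them.

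Two further places decide who contributes to these durations. Inclusion criterion 6 (section 2.4.3) reads "Alive during the ICU stay". Section 2.8.6 records "the mechanical ventilation duration time, LOS, total hospital stay" for patients who survive to ICU discharge and meet all six criteria. Section 2.8.7 then follows patients for up to one year after ICU admission or until death.

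**The concern.** In the primary composite, death is one of the events, so Kaplan-Meier is a sound description. In a length of stay the event is discharge, and death makes discharge impossible. The same approach is carried over without any provision for that change in the role of death.

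If deaths are censored, the curve treats the dead as patients who would later have been discharged at the same rate as those still in hospital. It therefore estimates discharge in a setting where nobody dies. If a death is taken as the end of the stay, it looks like an early discharge. Under either rule the reported discharge probability is not the share of patients who went home alive. The error grows with ward mortality, so unequal mortality distorts the group comparison as well. Unequal mortality is plausible here even without a treatment effect: under section 2.7 patients unsuitable for acupuncture, for example because of edema or coagulopathy, can enter the control group.

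**Working it through.** **Which durations are exposed.**

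| Outcome | Can an analysed patient die before the event? | Reason |
|---|---|---|
| Index ICU stay | No | Criterion 6 and section 2.8.6 limit the data to ICU survivors |
| Ventilation within that stay | No | Same |
| Hospital stay | Yes | ICU survival is required, survival to hospital discharge is not; section 2.8.7 follows patients to death |

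**Inputs.** The article states no mortality or discharge rate, and so no figure on this point to reproduce. Its sample size rests on incidences of 12.5% and 39.3% for another endpoint and does not bear on this. All rates below are assumptions.

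- Discharge hazard: l = 0.07 per day in both groups.
- Ward mortality: P, the eventual probability of dying before hospital discharge, from 0% to 10% as the main range.
- Constant hazards, so the death hazard is m = l × P / (1 − P).
- Horizon: t = 28 days of ward time at risk, with no other censoring.

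**Formulas.**

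- Deaths censored: 1 − KM = 1 − exp(−l·t).
- True share discharged alive: CIF = l / (l + m) × [1 − exp(−(l + m)·t)]. The first factor equals 1 − P.
- Death counted as end of stay: 1 − exp(−(l + m)·t).

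**Deaths censored.** 1 − exp(−0.07 × 28) = 1 − exp(−1.96) = 85.9%, whatever the mortality.

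| P | 1 − KM | True discharge alive | Overstatement (points) |
|---|---|---|---|
| 0% | 85.9% | 85.9% | 0 |
| 2% | 85.9% | 84.7% | 1.2 |
| 5% | 85.9% | 82.9% | 3.0 |
| 10% | 85.9% | 79.8% | 6.1 |

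Worked line for P = 10%: m = 0.07 × 0.10 / 0.90 = 0.00778; (l + m)·t = 0.07778 × 28 = 2.178; CIF = 0.90 × (1 − exp(−2.178)) = 0.90 × 0.8867 = 79.8%.

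The 0% row is the situation of index ICU stay and ventilation under the current text: no error.

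**Unequal mortality, deaths censored.**

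- 2% v 10%: true 84.7% v 79.8%, a difference of 4.9 points. 1 − KM shows 85.9% in both, a difference of zero.
- 5% v 15%: true 82.9% v 76.5%, a difference of 6.4 points, again shown as zero.

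**Death counted as end of stay, 2% v 10%.** For 2%, (l + m)·t = (0.07 / 0.98) × 28 = 2.00, giving 1 − exp(−2.00) = 86.5%. For 10% the figure is 88.7%. The group with more deaths appears to leave hospital sooner by 2.2 points, although its true share discharged alive is 4.9 points lower.

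**The case against.** **The article condenses a fuller plan.** It never says that death is censored, and rules for death in a secondary outcome are commonly left to the analysis plan. It is fair that censoring is an inference, and silence alone would be no finding. But the article does state a method, and neither simple reading of death makes the Kaplan-Meier discharge curve right. A coding that keeps the dead at risk as never discharged would work, but in substance that is already the competing-event estimate recommended here.

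**ICU stay and ventilation.** A reader might infer that all three durations are biased. The documents do not support that: ICU deaths lie outside these data. Restricting to ICU survivors raises a separate selection question, because treatment starts once criteria 1 to 5 are met and criterion 6 applies later. A competing-risks model fitted to survivors would not repair it.

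**Log-rank and Cox.** A reader might also infer that these tests are invalid. With deaths censored they remain valid comparisons of the cause-specific discharge hazard. In the illustration that hazard is equal in both groups, so a null test would be correct for it. What goes wrong is the Kaplan-Meier probability, and any reading of those tests as a comparison of how many patients were discharged.

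**Size.** This is one secondary outcome in a 98-patient pilot. With 49 per group the standard error of a difference between 84.7% and 79.8% is √[(0.847 × 0.153 + 0.798 × 0.202) / 49] = 7.7 points, larger than the 4.9 points hidden. Deaths also remain visible in the primary composite. This stands and keeps the point minor.

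**Conclusion.** The point holds for length of hospital stay. Carrying Kaplan-Meier over to it misstates the probability of discharge alive whenever some patients die on the ward. Equal mortality in the two groups does not remove the overstatement; unequal mortality additionally distorts the comparison.

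On assumed ward mortality of 2% to 10% and a discharge hazard of 0.07 per day, the overstatement at day 28 is about 1 to 6 points, and 2% v 10% would hide a 4.9-point difference. These figures illustrate scale only; the true size cannot be computed from the article.

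Index ICU stay and ventilation within it would be affected only if ICU deaths were retained. The primary composite is not affected. This is a worthwhile improvement, not a threat to the trial's main conclusions.

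**What to change.** In section 2.10, replace the general extension with a specific statement:

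- For length of hospital stay, death before discharge is a competing event. Report the cumulative incidence of discharge alive by group, compared with Gray's test.
- Describe any log-rank or Cox result with deaths censored as a comparison of cause-specific discharge hazards, not of discharge probabilities.
- Apply the same treatment to ICU stay and ventilation duration if ICU deaths are retained in the analysis.
- Keep Kaplan-Meier and log-rank for the composite of death or readmission.

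For hospital stay the cost is a sentence or two and standard software. Total hospital stay is already recorded for ICU survivors, and follow-up already runs to death. Extending the approach to ICU stay and ventilation is not free of new data: section 2.8.6 would have to provide for recording these durations in patients who die in the ICU.
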